#### Technical Performance

Technical performance on the simulator for each group will be determined by comparing the scores from the DOPS and GiECAT. Specifically, a mixed factor 2 (control curriculum versus intervention curriculum) times 3 (pre-test, post-test, delayed test) ANOVA will be used to determine whether there is a difference based on the rating scales. The Tukey HSD test will be used as a post-hoc analysis to determine any significant differences.

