#### Training Intervention

Participants are subsequently randomized using a randomization algorithm to 1 of 2 groups (control and intervention), following a 1:1 allocation distribution.

The control group receives 4 hours of interactive, small-group, didactic and hands-on sessions on the theory of colonoscopy, led by an expert academic gastroenterologist. The core curriculum was designed based on the American Society for Gastrointestinal Endoscopy (ASGE) colonoscopy curriculum and a detailed endoscopic training textbook and includes teaching on anatomy, pathophysiology, indications, risks and benefits of the procedures, training on specific elements of performance of colonoscopy procedures (eg, one-handed steering), and strategies for loop reduction, terminal ileal cannulation, and adequate visualization of mucosa [12,13]. This curriculum has been shown to be effective when compared to self-regulated learning on the simulator [3]. The sessions are interlaced with 6 hours of expert-assisted instruction on both the low-fidelity simulator (1 hour) and on the high-fidelity VR simulator (5 hours). Six modules of increasing difficulty in colonoscopy and colonoscopy polypectomy are taught with one-on-one feedback from an expert academic endoscopist. The endoscopy instructor demonstrates techniques, answers questions, and provides individualized performance feedback on global performance. The final 2 hours spent on the high-fidelity scenario use the integrated scenario, which features an SP and SN.

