### Outcome Measures

The primary outcome measure is the difference in performance between the control and intervention groups during participants’ 2 clinical colonoscopies. Each videotaped clinical colonoscopy will be independently assessed by 2 experienced endoscopists using the Joint Advisory Group for GI Endoscopy Direction Observation of Procedural Skills (JAG DOPS) (Multimedia Appendix 4) [15]. The raters will be blinded to the group assignment. Training on how to use the tool will be provided for raters by the investigators of the study.

Secondary outcome measures include the differences between the control and intervention groups with respect to (1) procedural knowledge, as assessed by the knowledge MCQ tests; (2) NTS performance during the clinical colonoscopies, as assessed by the Modified Objective Structured Assessment of Non-Technical Skills (M-OSANTS) for colonoscopy, which has been previously validated for surgery and modified for endoscopy [4] (Multimedia Appendix 5); (3) clinical performance on clinical colonoscopies, as assessed by the Gastrointestinal Endoscopy Competency Assessment Tool (GiECAT) [16] (Multimedia Appendix 6); (4) technical performance on a VR simulated colonoscopy after training and 4 to 6 weeks after training (immediate and delayed post-training assessments, respectively), as assessed by the JAG DOPS and the GiECAT; (5) technical and non-technical performance during an integrated scenario format test 4 to 6 weeks after training, as assessed by the JAG DOPS, GiECAT, and M-OSANTS; (6) patient comfort during the clinical colonoscopies, as assessed by the Nurse-Assessed Patient Comfort Score (NAPCOMS) [17] (Multimedia Appendix 7); (7) participant self-efficacy, as measured by an adapted scale based on the General Self-Efficacy Scale (GSE) [18,19] (Multimedia Appendix 8); and (8) global performance and communication skills during integrated scenarios as assessed by the Integrated Scenario Global Rating Form (ISGRF) and Integrated Scenario Communication Rating Form (ISCRF) [11,20,21], respectively (Multimedia Appendices 9 and ).

Experienced endoscopists will assess participants’ colonoscopy-specific skills, technical skills, and NTS during the pre-training, immediate, and delayed post-training simulation-based assessments.

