#### Non-Technical Performance

Non-technical performance on the simulator for each group will be determined by comparing the scores from the M-OSANTS, ISGRF, and ISCRF. Specifically, a mixed factor 2 (control curriculum versus intervention curriculum) times 3 (pre-test, post-test, delayed test) ANOVA will be used to determine whether there is a difference based on the rating scales. The Tukey HSD test will be used as a post-hoc analysis to determine any significant differences.

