### Self-Efficacy

Self-efficacy during the simulated setting for each group will be determined by comparing the scores from the GSE. Specifically, a mixed factor 2 (control curriculum versus intervention curriculum) times 3 (pre-test, post-test, delayed test) ANOVA will be used to determine whether there is a difference based on the rating scales. The Tukey HSD test will be used as a post-hoc analysis to determine any significant differences.

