### Sample Size Estimation

A power analysis was computed using G*Power version 3.1.9 [22]. Using a previous study that evaluated an NTS training curriculum in surgery, we conducted the analysis using the relevant effect size [4]. Based on an effect size of f=0.65, an alpha of .05 (2-tailed), a beta of .20, 2 groups, and 3 measurements, 16 participants are required to achieve a power of greater than 0.80 using repeated measures ANOVA (between-factors). Furthermore, a previous study comparing a curriculum in endoscopic simulation found that a minimum of 15 participants per group was sufficient to detect a significant difference [3]. To accommodate for a projected 20% dropout and/or non-response, we recruited a total of 42 participants.

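### The 2×3 ANOVAs for the secondary simulator and self-efficacy outcomes treat the pre-randomisation pre-test as an outcome level, which dilutes the arm effect and costs power that a covariate would recover

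*Protocol article*

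**What the plan says.** The Pre-Test section describes a baseline assessment. The next section, Training Intervention, opens with "Participants are subsequently randomized using a randomization algorithm to 1 of 2 groups", so the pre-test comes before allocation.

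Three analysis sections then make the pre-test one of three levels of the outcome:

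- Technical Performance (DOPS and GiECAT on the simulator): "a mixed factor 2 (control curriculum versus intervention curriculum) times 3 (pre-test, post-test, delayed test) ANOVA will be used".
- Non-Technical Performance: "Non-technical performance on the simulator for each group will be determined by comparing the scores from the M-OSANTS, ISGRF, and ISCRF", with a factor "times 3 (pre-test, post-test, delayed test) ANOVA will be used to determine whether there is a difference based on the rating scales".
- Self-Efficacy: "Self-efficacy during the simulated setting for each group will be determined by comparing the scores from the GSE", with the same 2×3 model.

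Each section adds Tukey HSD as post-hoc analysis. None says whether the group main effect or the group-by-time interaction is the test of interest.

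Outcome Measures places secondary outcome 4 after training: "technical performance on a VR simulated colonoscopy after training and 4 to 6 weeks after training". It places outcome 5, the integrated scenario scored on DOPS, GiECAT and M-OSANTS, at the delayed test only.

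Sample Size Estimation gives "Based on an effect size of f=0.65, an alpha of .05 (2-tailed), a beta of .20, 2 groups, and 3 measurements" and concludes that "16 participants are required to achieve a power of greater than 0.80 using repeated measures ANOVA (between-factors").

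**The concern.** Randomisation makes the expected arm difference at the pre-test zero. Entering that score as an outcome level has two effects. The group main effect averages a known zero with the two post-training differences. What remains of the signal moves to an interaction with two degrees of freedom, one of which is spent on change between the post-test and the delayed test.

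For outcomes 4 and 5 neither F test estimates the quantity that Outcome Measures defines. A real training effect could be understated if read from the main effect, or missed for want of power, although the pre-test score that would sharpen the comparison is already part of the data.

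**Working it through.** **Inputs from the protocol article.** f=0.65, two-sided alpha 0.05, 2 groups, 3 measurements, 16 participants (Sample Size Estimation); 19 control and 23 NTS participants (Results). For two equal groups d = 2f = 1.3.

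**Assumptions.** The article gives no correlation between tests. I take equal correlation ρ between all pairs, 0.5 as the central value and 0.2 to 0.8 as the range. Unless stated otherwise the true arm differences at pre-test, post-test and delayed test are (0, d, d) in SD units. Power is from the noncentral F distribution, with h = n₁n₂/N.

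**Step 1: reproduce the plan's figure.** For the between-groups effect with the full difference at all three measurements, λ = h·d²/((1+2ρ)/3) with 1 and N−2 df. With 8 per group, h = 4, and at ρ=0.5, λ = 4 × 1.69/0.667 = 10.14, giving power 0.841. With 14 participants power is 0.781. The stated 16 is therefore reproduced, for an effect assumed present at every measurement, including the pre-test.

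**Step 2: dilution.** The main effect estimates (0 + d + d)/3 = 2d/3, one third less than the post-training difference. This needs no value of ρ, only equal effects at the two later tests.

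**Step 3: formulas with no effect at the pre-test.**

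- Group main effect: λ = h(2d/3)²/((1+2ρ)/3); 1 and N−2 df.
- Interaction: squared deviations of (0, d, d) from their mean sum to (4/9 + 1/9 + 1/9)d² = 2d²/3, so λ = h(2/3)d²/(1−ρ); 2 and 2(N−2) df.
- ANCOVA on the mean of the two later scores: λ = h·d²/((1+ρ)/2 − ρ²); 1 and N−3 df.
- ANCOVA at one later time: λ = h·d²/(1−ρ²); 1 and N−3 df.

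**Step 4: the plan's 16 participants, d=1.3, ρ=0.5.** The main-effect λ falls from 10.14 to 10.14 × 4/9 = 4.51, and power from 0.841 to 0.507. The interaction has 0.722. ANCOVA on the mean has 0.90 to 0.92, with or without an allowance for chance baseline imbalance.

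**Step 5: the recruited 19 v 23**, h = 19 × 23/42 = 10.405.

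| d | ρ | Main effect | Interaction | ANCOVA, mean of two | ANCOVA, one time |
|---|---|---|---|---|---|
| 1.3 (plan) | 0.2 | 0.98 | 0.93 | 1.00 | 0.99 |
| 1.3 (plan) | 0.5 | 0.92 | 0.99 | 1.00 | 1.00 |
| 1.3 (plan) | 0.8 | 0.83 | 1.00 | 1.00 | 1.00 |
| 0.65 (assumed) | 0.3 | 0.46 | 0.42 | 0.78 | 0.57 |
| 0.65 (assumed) | 0.5 | 0.39 | 0.56 | 0.82 | 0.66 |
| 0.65 (assumed) | 0.7 | 0.33 | 0.79 | 0.93 | 0.82 |

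At the plan's effect, the loss against ANCOVA on the mean is 1.00 − 0.98 = 0.02 to 1.00 − 0.83 = 0.17 for the main effect, and 0 to 1.00 − 0.93 = 0.07 for the interaction.

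**Step 6: an effect that fades.** If the effect is present only at the post-test (d=0.8, ρ=0.5), the interaction has power 0.748 and ANCOVA on the averaged later scores 0.420. Averaging is not always the better choice.

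**The case against.** The strongest reply is that a group-by-time interaction is a valid test of whether the arms change differently, and that the choice between it and ANCOVA concerns efficiency. That stands: under the null each test, taken alone, holds its 5% level. At high correlation the interaction is not weak. At d=0.65 and ρ=0.7 it has 0.79, against 0.82 for ANCOVA at one time.

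The delayed test exists to study retention, so sensitivity to fading is not wasted, as Step 6 shows. Tukey comparisons might also bring out arm differences at single times, though the pairs are not listed. Which F test is decisive may be settled in a fuller plan. The time-point mismatch reaches outcomes 4 and 5 only; self-efficacy and the two integrated-scenario rating forms carry no post-training restriction.

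A reader might infer that the design loses half its power. The documents do not support that. Their 0.65 is f, not d; at d=1.3 with 42 participants the loss is modest, and a loss near half needs a smaller assumed effect. Nor do they support a reading that the trial is too small: Step 4 shows that 16 would fall short for the diluted main effect, but 42 were recruited and completed.

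What survives the reply is that the pre-test is fixed as an outcome level, and that the main effect, the one the sample size was computed for, is the diluted one.

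**Conclusion.** The point holds as a matter of efficiency and of a blurred target of estimation, for secondary outcomes only. The one-third dilution of the main effect is exact when the effect is equal at both later tests. The power cost is conditional. At the plan's own effect with 19 v 23 it is about 2 to 17 points (main effect) or 0 to 7 points (interaction) for ρ from 0.2 to 0.8. At an assumed d=0.65 and ρ=0.5, the interaction is about 26 points below ANCOVA on the post-training mean (0.82 − 0.56) and 10 points below ANCOVA at one time (0.66 − 0.56); the main effect is about 43 and 27 points below. The single-time figure is the relevant one for outcome 5. All of these rest on equal correlations and, except in Step 6, a sustained effect.

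The primary analysis of the two clinical colonoscopies is a 2×2 ANOVA without a pre-test level and is not touched. This is a worthwhile improvement, not a defect that threatens the trial's main conclusion.

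**What to change.** For each scale in the three sections, replace the 2×3 ANOVA by a model of the post-test and delayed scores with arm, time, arm-by-time and the pre-test score of the same instrument as covariate, allowing for the repeated measures within participant. Report the adjusted between-arm difference with its 95% CI at the post-test and at the delayed test. For outcome 5 use the delayed score alone, adjusted for the pre-test. Reporting each time separately also covers an effect that fades.

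The cost is a change of analysis wording. The pre-test is already part of the design, no new data are needed, and the models run in the same software. The article describes assessment and analysis as still in progress, so the change should be dated and recorded as made before the arms are compared.

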#### Non-Technical Performance

Non-technical performance on the simulator for each group will be determined by comparing the scores from the M-OSANTS, ISGRF, and ISCRF. Specifically, a mixed factor 2 (control curriculum versus intervention curriculum) times 3 (pre-test, post-test, delayed test) ANOVA will be used to determine whether there is a difference based on the rating scales. The Tukey HSD test will be used as a post-hoc analysis to determine any significant differences.

### Self-Efficacy

Self-efficacy during the simulated setting for each group will be determined by comparing the scores from the GSE. Specifically, a mixed factor 2 (control curriculum versus intervention curriculum) times 3 (pre-test, post-test, delayed test) ANOVA will be used to determine whether there is a difference based on the rating scales. The Tukey HSD test will be used as a post-hoc analysis to determine any significant differences.

### Sample Size Estimation

A power analysis was computed using G*Power version 3.1.9 [22]. Using a previous study that evaluated an NTS training curriculum in surgery, we conducted the analysis using the relevant effect size [4]. Based on an effect size of f=0.65, an alpha of .05 (2-tailed), a beta of .20, 2 groups, and 3 measurements, 16 participants are required to achieve a power of greater than 0.80 using repeated measures ANOVA (between-factors). Furthermore, a previous study comparing a curriculum in endoscopic simulation found that a minimum of 15 participants per group was sufficient to detect a significant difference [3]. To accommodate for a projected 20% dropout and/or non-response, we recruited a total of 42 participants.

## Results

A total of 42 participants were recruited, randomized, and completed the study. No participants were lost to follow-up. Through a 1:1 allocation distribution, 19 individuals were randomized into the control group and 23 individuals were randomized into the NTS group. Their demographic information and endoscopic experiences are summarized in Table 1. Two experienced endoscopists were recruited to assess participants’ videotaped performances and we anticipate completion of all assessments by August 2017. Data analysis, manuscript writing, and subsequent submission for publication is expected to be completed by December 2017.

**Table 1 table1:** Baseline demographic characteristics and endoscopy experience of participants (N=42).

Variable		Control group (n=19)	Intervention (NTS^a^) group (n=23)
Age in years, mean (SD)		29.5 (1.8)	28.1 (2.1)
**Gender, n (%)**			
	Male	11 (58)	16 (70)
	Female	8 (42)	7 (30)
**Training program, n (%)**			
	Gastroenterology	4 (21)	6 (26)
	General surgery	13 (68)	16 (70)
	Internal medicine	2 (11)	1 (4)
**Previous endoscopic experience, mean (SD)**			
	Number of independent colonoscopies	0.11 (0.46)	0.30 (0.82)
	Number of assisted colonoscopies	2.63 (4.66)	1.70 (2.50)

^a^NTS: non-technical skills.

## Discussion

### Principal Findings

The practice of effective NTS is critical in procedural medicine. In addition, deficiencies in NTS are associated with adverse patient outcomes [5,6]. However, there is evidence that NTS training can improve surgical performance in the simulated setting, lead to better attitudes towards patient safety, and promote more self-reflection among trainees [4,23,24].

Previous studies have explored NTS in GI endoscopy. Matharoo et al shared their perspectives on implementing an endoscopy safety checklist to decrease adverse health outcomes [25]. This paper reported on the implications, logistics, and uptake of a safety checklist, and did not present any outcome data. A 2014 report implementing an NTS curriculum found that it improved patient safety knowledge and attitudes among multi-disciplinary endoscopy teams [24]. In another study, an RCT comparing 2 curricula of SBT in endoscopy found that improved NTS in the simulated setting were associated with superior clinical performance [3]. However, that study did not test NTS training as an intervention.

### Conclusion

This study aims to evaluate the direct impact of NTS training on clinical colonoscopy performance. Results can inform the potential implementation of NTS into postgraduate gastrointestinal curricula.

## Appendix

Multimedia Appendix 1 Baseline demographic and endoscopic experience.

Multimedia Appendix 2 Knowledge test questions.

Multimedia Appendix 3 Endoscopic non-technical skills (E-NTS) checklist.

Multimedia Appendix 4 Joint Advisory Group on GI Endoscopy Direct Observation of Procedural Skills (JAG DOPS) form.

Multimedia Appendix 5 Modified Objective Structured Assessment of Non-Technical Skills (M-OSANTS) form.

Multimedia Appendix 6 Gastrointestinal Endoscopy Competency Assessment Tool (GiECAT) form.

Multimedia Appendix 7 Nurse Assessed Patient Comfort Score (NAPCOMS) form.

Multimedia Appendix 8 General self-efficacy assessment.

Multimedia Appendix 9 Integrated Scenario Global Rating Form (ISGRF).

Multimedia Appendix 10 Integrated Scenario Communication Rating Form (ISCRF).

## Abbreviations

ANOVA: analysis of variance
E-NTS: endoscopic non-technical skills
GI: gastrointestinal
GiECAT: Gastrointestinal Endoscopy Competency Assessment Tool
GSE: General Self-Efficacy Scale
HSD: honest significant difference
ISCRF: Integrated Scenario Communication Rating Form
ISGRF: Integrated Scenario Global Rating Form (ISGRF)
JAG DOPS: Joint Advisory Group for GI Endoscopy Direction Observation of Procedural Skills
M-OSANTS: Modified Objective Structured Assessment of Nontechnical Skills
MCQ: multiple choice questions
NAPCOMS: Nurse-Assessed Patient Comfort Score
NTS: non-technical skills
RCT: randomized controlled trial
SBT: simulation-based training
SN: standardized nurse
SP: standardized patient
VR: virtual reality
